#### Descriptive characteristics

We will report baseline characteristics for individual participants with CRPS such as affected limb, type of inciting injury, CRPS duration, co-morbidities, prescribed medications and other treatments, and change in handedness score.

Minimisation factors listed in Table 2 will be presented as group means for continuous factors or proportion of participants in each group who are classed positive on each categorical factor. We will conduct a series of contrasts and chi-square tests to confirm that the minimisation procedure successfully equated the two groups on these factors. Contrasts will also be used to confirm that the PA and sham treatment groups are matched on mean Profile of Mood States, Tampa Scale for Kinesiophobia, Revised Life Orientation Test, and Patient Centred Outcomes Questionnaire scores.

#### Efficacy of PA treatment in reducing pain and CRPS symptom severity (RQ1)

A 2 × 6 ANOVA with Group as a between-subjects factor (PA treatment, sham treatment), and Time (RS1, RS2, RS3, RS4, LTFU1, LTFU2) as a within-subject factor will be conducted for the first primary outcome of pain intensity rating. We will also conduct sixteen a-priori contrasts to compare RS1 vs. RS2, RS2 vs. RS3, RS3 vs. RS4, RS2 vs. RS4, RS2 vs. LTFU1, RS4 vs. LTFU1, LTFU1 vs. LTFU2, and RS2 vs. LTFU2 within each group. We will also conduct a 2 × 4 ANOVA with the factors Group (PA treatment, sham treatment) and Time (RS1, RS2, RS3, RS4) for the second primary outcome of CPRS severity score, followed by eight a-priori contrasts comparing RS1 vs. RS2, RS2 vs. RS3, RS3 vs. RS4, and RS2 vs. RS4 within each group. We are primarily interested in detecting any changes between RS2 and RS3 which would represent immediate effects of treatment.

Minimisation factors (see Table 2) may be included as covariates in the ANOVAs if there are significant differences at RS1. Similarly, if we find significant group differences in the Profile of Mood States, Tampa Scale for Kinesiophobia, or Revised Life Orientation Test RS1 scores, these variables may be used as covariates in the ANOVAs on pain and CRPS severity score.

We will also calculate the Number Needed to Treat (NNT) separately for pain and CRPS severity score. The NNT will be based on the proportion of participants in each treatment arm that achieved clinically significant pain relief (≥2 points on 0–10 NRS scale [110]) and reduction in CRPS symptom severity (≥4.9 points [35]) in RS3 compared to RS2.

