## Methods

### Design

The trial was prospectively registered [33] and Additional file 1 lists all items from the World Health Organisation Trial Registration Data Set. This study has a double-blind, randomized, sham-controlled design. The schedule of enrolment, interventions, and assessments is presented in Table 1 and consists of four in-person Research Sessions (RS), 2 weeks of twice-daily home-based treatment, and two sets of long-term postal follow-up questionnaires. After provisional eligibility assessment through a structured phone interview, 42 participants with CRPS will undergo two baseline research sessions. Two baseline assessments (RS1 and RS2) are conducted to give an indication of normal fluctuations in CRPS symptoms (or lack thereof) prior to the treatment period. This will allow us to assess whether any change over the treatment period is meaningful, that is, greater than baseline fluctuations.^1^ Research Session 1 (RS1) commences the timeline of the study at week 1 and includes in-person assessment of the eligibility criteria, informed consent, and collection of the outcome measures that are described in the “Measurements” section. Treatment allocation takes place 1–5 days before Research Session 2 (RS2), where the participants with CRPS are randomly allocated to one of the two groups of equal size: the PA treatment group or the sham treatment group. RS2 at the end of week 4 involves revisiting eligibility criteria and collecting outcome measurements. Immediately after completing RS2, the participants are instructed in how to carry out the treatment by a researcher who is not involved in any part of data collection. They then perform their first treatment under the guidance of that researcher. All other elements of the study (telephone screening, symptom assessment, experiment administration, and input of questionnaire data) are performed by researchers who are blind to the conditions that the participants have been allocated to. The treatment period spans weeks 5 and 6 of the study, where the participants perform twice-daily treatment in a self-guided manner. Outcome measurements are collected in two post-treatment assessments (RS3 and RS4) to evaluate differences in PA versus sham treatment effects, and whether any benefits of treatment are maintained at 4 weeks after treatment. The first post-treatment Research Session (RS3) takes place at the beginning of week 7 (i.e., the day immediately following the final treatment session). Research Session 4 (RS4) takes place in the beginning of week 11. Each research session is expected to last between 2 and 4 h, including breaks between the assessments. During the first 10 weeks of the study, the participants also record their self-reported daily ratings of pain intensity, range of movement, and the extent to which their symptoms interfere with daily life in a provided logbook, which will allow us to track the time course of any changes between research sessions. Long Term Follow-Up 1 at 3 months (LTFU1; week 19) and Long Term Follow-Up 2 at 6 months (LTFU2; week 31) post-treatment are conducted through questionnaires sent and returned by post. RS3 marks the primary endpoint and LTFU2 marks the secondary and final endpoint of the study.

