#### Primary outcomes

A change between RS2 (immediately before the commencement of treatment) and RS3 (immediately after the end of the treatment period) in current self-reported pain intensity and CRPS severity score [35, 52] are the primary outcomes. People with CRPS consider pain relief to be the highest priority for recovery [59], and pain intensity is the most common primary outcome in chronic pain trials [60]. Current pain intensity is measured using item 6 of the Brief Pain Inventory (BPI; short form) [42], which is a Numerical Rating Scale (NRS) ranging from 0 – “no pain” to 10 – “pain as bad as you can imagine”. The BPI has high reliability [42]. In addition to pain, CRPS involves a range of other debilitating symptoms, some of which were also affected by PA in previous studies [22, 24]. Therefore, we included a comprehensive measure of symptoms severity as the second primary outcome. The CRPS severity score assessment protocol follows the 16-points scoring system published by Harden and colleagues [35]. This continuous index of CRPS symptom severity has good discrimination abilities, concurrent validity and adequate sensitivity to change [35, 52], and has been recommended as one of the core outcome measures for CRPS clinical studies [61].

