### Blinding

All outcome measurements are recorded by a researcher who is blind to group allocations (MH). A researcher ([name]) who is not involved in data collection allocates participants with CRPS to treatment groups 1–5 days before RS2. [name] or another researcher not involved in data collection ([name]) trains the participants in how to carry out the PA treatment or sham treatment in a self-guided manner at the end of RS2. The participants return the goggles in sealed opaque bags after completing the treatment in RS3 so that the primary researcher (MH) remains blind to their treatment allocation. MH will be unblinded as to the group allocations of the participants once the last person has completed RS4, as there will be no further research sessions in which she will assess symptoms. Follow-up measurements in weeks 19 (LTFU1) and 31 (LTFU2) will be carried out via postal questionnaires scored by research assistants who are blind to the group allocations.

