#### Timing

No interim analyses are planned. The timing of the final analyses will be stratified by planned length of follow-up for the relevant outcome measures. Once all participants have completed RS4, we will analyse the RS1-RS4 data to address our research questions regarding the efficacy of PA treatment in reducing CRPS symptom severity (RQ1) and the relationships between the severity of clinical symptoms of CRPS and neuropsychological changes in perception of and attention to the affected limb and its corresponding side of space in RS1 (RQ5). We will conduct separate analyses of current self-reported pain intensity, the BPI, the Pain Detect Questionnaire, the BPDS, the Tampa Scale for Kinesiophobia, the Profile of Mood States, and the Patient’s Global Impression of Change scores once all participants meet the secondary endpoint (LTFU2). Recruitment will be terminated if we are not able to collect 42 full datasets for RS1-RS4 by 1 March 2019.

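### The only between-group test of the pain primary outcome includes the 3- and 6-month postal visits, although the endpoint is RS3, and the protocol does not say which pain result is confirmatory or when it is produced

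*Protocol article*

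**What the plan says.** **Endpoint.** Primary outcomes defines both primary outcomes, current pain and CRPS severity score, as "A change between RS2 (immediately before the commencement of treatment) and RS3 (immediately after the end of the treatment period"). Design states that "RS3 marks the primary endpoint and LTFU2 marks the secondary and final endpoint of the study". The sample size calculation is also built on the RS2–RS3 pain change.

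**Analysis.** Under RQ1, pain gets a 2 × 6 ANOVA with Group between subjects and "Time (RS1, RS2, RS3, RS4, LTFU1, LTFU2) as a within-subject factor will be conducted for the first primary outcome of pain intensity rating". It is followed by contrasts: "We will also conduct sixteen a-priori contrasts to compare RS1 vs. RS2, RS2 vs. RS3, RS3 vs. RS4, RS2 vs. RS4", and four further pairs that involve LTFU1 or LTFU2, all within each group. For the other primary outcome, CRPS severity, the text reads "We will also conduct a 2 × 4 ANOVA with the factors Group (PA treatment, sham treatment) and Time (RS1, RS2, RS3, RS4"), with eight within-group contrasts. The same section says that interest lies mainly in RS2–RS3, and it adds a number needed to treat based on RS3 against RS2.

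**Multiplicity and missing data.** Statistical analyses applies Holm-Bonferroni within each outcome analysis. Treatment outcome analyses carries the RS2 value forward for missing observations.

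**Timing.** The Timing section says "Once all participants have completed RS4, we will analyse the RS1-RS4 data to address our research questions regarding the efficacy of PA treatment"; the sentence goes on to specify reduction of CRPS symptom severity and tags this as RQ1. It then says "We will conduct separate analyses of current self-reported pain intensity, the BPI, the Pain Detect Questionnaire, the BPDS" and further questionnaires, once everyone has reached LTFU2. No interim analyses are planned.

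**Blinding.** The primary researcher is unblinded when the last participant completes RS4. Blinded assistants score the postal questionnaires, and participants stay blind until all data collection ends.

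**The concern.** The two primary outcomes share one endpoint, yet only severity has a between-group test that can be run on the RS1–RS4 data. The outcome that sized the trial has a test that takes in two later visits. Three consequences follow.

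1. **The primary pain test depends on data collected after its endpoint.** The Group × Time interaction pools six visits. A participant who does not return a postal form enters LTFU1 or LTFU2 with the RS2 value, so postal non-response feeds into a test meant to answer an RS2–RS3 question.
2. **The confirmatory pain result is not identified.** RQ1 covers pain as well as severity (Primary research question and hypothesis). If the RS4-cut analysis answers RQ1, pain belongs there, but no model that can be run at that cut is given for it. If pain is analysed only after LTFU2, RQ1 is half answered at RS4.
3. **Analysis choices stay open after the primary researcher is unblinded.** Covariates in the pain model are optional, and the switch from ANOVA to mixed models depends on a judgement of severe assumption violations. One of those assumptions is sphericity, which with six time levels partly reflects the postal data.

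**Working it through.** **Planned sample size, reproduced first.** Inputs from Sample size and power calculation: difference 2, SD 1.98, type I error 5% (two-sided assumed), power 90%.
n per arm = 2 × (1.96 + 1.2816)² × 1.98² / 2² = 20.6, rounded up to 21, so 42 in total. This matches the protocol. The point concerns the analysis, not this figure.

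**Calendar.** Inputs from Design: RS3 week 7, RS4 week 11, LTFU2 week 31.
- RS3 to LTFU2: 31 − 7 = 24 weeks.
- RS4 to LTFU2: 31 − 11 = 20 weeks.
- The notes to Table 1 allow up to 3 weeks' deferral of LTFU2 on top.

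**Contrast count for pain.** Eight pairs × 2 groups = 16. Pairs that involve a postal visit: RS2 v LTFU1, RS4 v LTFU1, LTFU1 v LTFU2 and RS2 v LTFU2. That is 4 × 2 = 8 of the 16. The other 8 are the set specified for severity.

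**First Holm step.** With all 16: 0.05/16 = 0.003125. With the RS1–RS4 contrasts only: 0.05/8 = 0.00625.

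**Within-arm RS2–RS3 contrast.** Paired t, n = 21, 20 degrees of freedom, two-sided, noncentrality = dz × √21. If 1.98 is taken as the SD of change (an assumption; the protocol says only that it comes from pain ratings), dz = 2/1.98 = 1.01.

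| dz | power at 0.00625 | power at 0.003125 |
|---|---|---|
| 1.01 (planning values) | 0.93 | 0.88 |
| 0.8 (assumed) | 0.72 | 0.62 |
| 0.6 (assumed) | 0.41 | 0.31 |

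These are first-step thresholds, the strictest that Holm applies.

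**Between-group interaction.** Assumptions: 21 per arm, SD 1.98 at each visit, sphericity, a 2-point group difference at RS3 only, within-person correlation ρ. Noncentrality λ = 2n Σ(eₜ/2)² / [SD²(1 − ρ)], where eₜ is the group difference at visit t minus its mean over visits. Degrees of freedom are 3 and 120 for the 2 × 4 model, 5 and 200 for the 2 × 6 model.

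| ρ | 2 × 4 | 2 × 6 |
|---|---|---|
| 0.3 | 0.81 | 0.78 |
| 0.5 | 0.93 | 0.92 |
| 0.7 | 0.995 | 0.994 |

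If the difference fades to 1 point at RS4 and to none afterwards, the 2 × 6 model is slightly ahead (ρ = 0.5: 0.93 against 0.90). The extra visits hardly change omnibus power in either direction.

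**The timing statements side by side.** RQ1 is pain and severity. The RS4-cut sentence carries the RQ1 tag but names severity. The LTFU2 sentence lists current pain first and calls these analyses separate. One reading is severity at RS4 and pain once, after LTFU2. The other is pain at both cuts, the first with a model that the RQ1 section does not give. The text fits both and ranks neither.

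**The case against.** The best defence is that the Timing section is consistent. It stages the final analyses by each outcome's length of follow-up. Severity ends at week 11 and is named at the RS4 cut; pain runs to week 31 and is named at LTFU2. The 2 × 4 and 2 × 6 models then fit that staging, and the different time structures follow from severity needing an in-person examination. This is a fair reading, and an analysis plan not shown may confirm it. It does not remove the problem: the pain test still spans visits long after its stated endpoint, and the RQ1 tag at the RS4 cut still covers pain by the protocol's own definition.

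Four stronger readings are tempting, and the documents do not support them.

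- **Pain will be tested twice.** No 2 × 4 pain model or 8-contrast pain family appears anywhere. Double analysis is possible under the wording but is not planned by it.
- **The 2 × 6 ANOVA is the only pain analysis.** The RS2–RS3 contrasts and the number needed to treat use RS2 and RS3 alone. However, the contrasts are within-group, and the number needed to treat is given without a test.
- **Unblinding contaminates the pain data.** RS2 and RS3 ratings are self-reported and already recorded when the primary researcher is unblinded. Participants and the postal scorers stay blind. Only analysis decisions are exposed.
- **The trial loses substantial power.** At the planning values the loss is small, it concerns within-arm contrasts that do not test the between-group hypothesis, and a larger Holm family is conservative. Nor does a missing postal form remove anyone from the intention-to-treat model or alter a raw RS2–RS3 contrast.

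**Conclusion.** The point holds as a problem of specification and timing. The pain primary outcome is an RS2–RS3 change, but its only between-group test needs data scheduled up to 24 weeks later, with RS2 values filling missing forms, and cannot be run at the RS4 cut. The protocol leaves open whether pain waits or is analysed at both cuts, and which result is confirmatory. Meanwhile the primary researcher is unblinded with discretionary choices in the pain model still to be made.

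The numerical cost is modest. The first Holm step is halved, and within-arm power is 0.88 instead of 0.93 if 1.98 is the SD of change. Interaction power is 0.78–0.994 instead of 0.81–0.995 for within-person correlations of 0.3 to 0.7, with sphericity and an effect at RS3 only. The change is worth making because it is cheap and leaves one identified primary pain result.

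**What to change.** - In the RQ1 analysis section, make the primary pain analysis Group × Time over RS1–RS4, as for CRPS severity. Run it once, at the RS4 cut, with Holm over the eight RS1–RS4 contrasts only.
- Move the pain model and contrasts involving LTFU1 and LTFU2 to RQ3 as a secondary analysis, with its own Holm family, run after LTFU2.
- In Timing, name pain alongside severity at the RS4 cut, and state that this is the only primary pain result.

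The cost is wording only: no visits, data or participants change. The small downside is that long-term pain is reported in a separate secondary analysis, outside the primary error control. The change removes the 20-week gap between unblinding of the primary researcher and the primary pain analysis. It does not by itself settle the optional covariates or the switch to mixed models.

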### Statistical analyses

To process and analyse the data we will use IBM SPSS Statistics [106], R [107], and MATLAB [108] software. Hypotheses will be tested using a significance level of *α* = .05. We will control type I errors in the primary analyses using Holm-Bonferroni corrections for multiple comparisons within each outcome analysis. No correction for multiple testing will be made in the exploratory analyses. We will report 95% bias-corrected and accelerated (BCa) bootstrap confidence intervals around all mean values.

Outliers are defined as scores outside ±3 SDs from the participant’s mean score for a task condition (participant-level data) or from the group mean (group-level data) for a particular test or task condition. We will examine participant-level and group-level RT data in the Hand Laterality Recognition and Directional Hypokinesia tasks for the presence of outliers and use nearest neighbour replacement if any are identified. We will use the same method of nearest neighbour replacement for the group-level outliers identified on the remaining outcome measures.

T-tests and ANOVAs will be conducted to compare mean values between groups and between data collection time points. Statistically significant interactions will be interrogated through follow-up contrasts. Wilcoxon signed-rank tests and Mann-Whitney U tests will be used if assumptions of t-tests are violated; however, ANOVAs are robust to moderate violations of normality and homogeneity of variance. Therefore, we will use ANOVAs unless severe violations of normality, homogeneity of variance, and sphericity assumptions are present, in which case we will use linear mixed models analyses with bootstrapping procedures.

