#### Sample size and power calculation

The required sample size was calculated based on the primary outcome measure of self-reported pain [109]. A meta-analysis defined a clinically significant reduction in pain as a change of Δ = − 2 (on a scale of 0–10) [110]. The sample size required to detect a pain reduction of this magnitude between RS2 and RS3 was estimated. The risk of type I error was set at 5% and the risk of type II error was set at 10%, giving 90% power to detect a significant change in the pain. The standard deviation expected in the current study was estimated as 1.98 based on pain intensity ratings obtained by our group in recent research [8]. Given these parameters, a minimum of 42 participants with CRPS (21 per group) is required to evaluate the effects of the PA treatment on the primary outcome measure of pain. Taking into account an anticipated drop-out rate of 20%, up to 52 participants with CRPS will be enrolled in order to obtain a total of at least 21 complete datasets for RS1-RS4 per treatment group. To provide normative data, 21 healthy (pain-free) control participants will be recruited.

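### The primary RS2-RS3 comparison shares a Holm family with pre-treatment, follow-up and sham-arm contrasts, so it can face a threshold as low as .0031 (pain) or .00625 (severity), while the sample size assumes one test at .05

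*Protocol article*

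**What the plan says.** Under Primary outcomes, the endpoint for both current pain and CRPS severity is "A change between RS2 (immediately before the commencement of treatment) and RS3 (immediately after the end of the treatment period". The RQ1 efficacy section confirms the emphasis: "We are primarily interested in detecting any changes between RS2 and RS3 which would represent immediate effects of treatment".

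The same section plans a Group x Time ANOVA for each outcome and then a list of contrasts. For pain: "We will also conduct sixteen a-priori contrasts to compare RS1 vs. RS2, RS2 vs. RS3, RS3 vs. RS4, RS2 vs. RS4", ending with "LTFU1 vs. LTFU2, and RS2 vs. LTFU2 within each group". For CRPS severity the ANOVA is "followed by eight a-priori contrasts comparing RS1 vs. RS2, RS2 vs. RS3, RS3 vs. RS4, and RS2 vs. RS4 within each group".

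The multiplicity rule, under Statistical analyses, is: "We will control type I errors in the primary analyses using Holm-Bonferroni corrections for multiple comparisons within each outcome analysis". The general level is given there too ("Hypotheses will be tested using a significance level of" .05). Neither section takes RS2-RS3 out of the corrected set, ranks it first or gives it its own alpha.

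Under Sample size and power calculation, the trial is sized for the RS2-RS3 change in pain: "The risk of type I error was set at 5% and the risk of type II error was set at 10" per cent. That section does not mention a multiplicity adjustment.

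**The concern.** A comparison declared primary would normally be tested at the level used to size the trial. Read literally, this plan corrects it jointly with contrasts that answer other questions. RS1 vs. RS2 precedes treatment and gauges baseline fluctuation. The RS4 and postal follow-up pairs concern durability. Half of the contrasts describe change in the sham arm alone.

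What is at stake is power, not false positives. The primary comparison may pay for contrasts that are not the primary question, and the printed 90% belongs to a threshold that the plan does not guarantee. A real effect of the planned size could then miss significance because of how the family was drawn.

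**Working it through.** **Inputs from the protocol.** Difference 2 points on the 0-10 scale; SD 1.98; 21 per group; alpha .05; power 90%; 16 pain contrasts and 8 severity contrasts. **Not in the protocol:** the SD of the RS2-RS3 change, or the RS2-RS3 correlation (rho).

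**1. Reproduce the sample size.** Two-sided, two-sample normal approximation:

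n per group = 2 x (1.960 + 1.282)² x 1.98² / 2² = 20.6, rounded up to 21, so 42 in total.

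This matches. A one-sided test would give 17 per group. At 21 per group, power is 90.5% by the normal approximation and 89.1% by noncentral t. The printed figure therefore uses unadjusted .05.

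**2. Count the family.** For pain, each arm has one pre-treatment pair (RS1-RS2), the RS2-RS3 pair and six pairs involving later visits: 8 pairs x 2 arms = 16. For severity, 4 pairs x 2 arms = 8.

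**3. Strictest Holm step.** Pain: .05/16 = .003125. Severity: .05/8 = .00625. Holm relaxes towards .05 as smaller p-values are rejected, so these are the lower limits of the threshold.

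**4. Power of the listed within-group pain contrast.** Take the SD of change as 1.98 x √(2(1 − rho)), n = 21, paired t on 20 df, with noncentrality 2√21 / SD of change:

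| rho (assumed) | SD of change | Power at .05 | Power at .003125 |
|---|---|---|---|
| 0 | 2.80 | 87.5% | 48.6% |
| .3 | 2.34 | 96.1% | 70.1% |
| .5 | 1.98 | 99.3% | 87.7% |
| .6 | 1.77 | 99.8% | 94.9% |
| .7 | 1.53 | about 100% | 99.0% |

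Power at the first step reaches 90% at a correlation of about .53.

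**5. Does the step-down help?** The full 16-contrast Holm procedure was simulated with 3,000 runs per scenario, equal correlation between visits, SD 1.98 at each visit, no change under sham, and a 2-point PA effect at RS3 only, at RS3 and RS4, or sustained. Power for the PA-arm RS2-RS3 contrast was about 48-49% at rho 0, 71-72% at rho .3 and 88% at rho .5. These are close to the first-step values in every scenario, so the step-down recovers little.

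**6. The sizing section's own two-sample basis.** If a between-arm contrast were held to .003125 at 21 per group, power would be 62.5% by the normal approximation (36 per group needed for 90%) or 55.6% by noncentral t (38 per group). This is conditional: the listed family contains no between-arm contrast.

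**The case against.** Several points on the other side are sound.

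- **The two-sample figures are tempting but are not the plan's power.** A reader might infer that the trial has only 56% power, or needs 38 per arm. The documents do not support that. All sixteen pain contrasts are within group. The between-arm question is carried by the Group x Time ANOVA, and nothing assigns .0031 to that test. Part of the gap between 56% and the printed 90% is also method: noncentral t gives 89% before any correction.
- **The loss may be negligible.** It turns on a correlation that the protocol does not give. If the contrasts use a pooled ANOVA error (assumed compound symmetry, 200 df), power at .0031 is 82% at rho .3 and 95% at rho .5.
- **RS2-RS3 need not have the smallest p-value, even if the effect peaks at RS3.** In the simulation it did so in about 46-49% of runs with an RS3-only effect and 23-25% with a sustained one. The power loss nevertheless persists, as step 5 shows.
- **The correction is conservative, not invalid.** Holm holds under any dependence. That six visits allow only five independent contrasts per arm is therefore no fault of validity. The other contrasts also have stated purposes.
- **Family membership is inferred.** The article does not say whether the ANOVA terms belong to the family, and an analysis plan may settle this. But the wording it does print puts all contrasts of an outcome together and exempts none.

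What remains is the mismatch between the stated correction and the stated sizing.

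**Conclusion.** The concern holds as a mismatch between sections. RS2-RS3 is primary in two places, yet the printed multiplicity rule places it among 16 contrasts for pain and 8 for severity, while the sizing assumes one test at .05. The threshold can be as low as .0031 or .00625; it is not bound to be.

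The cost for the listed pain contrasts depends on the assumed RS2-RS3 correlation: first-step power is about 49% at 0 and 99% at .7. It rests on the protocol's 2 points, SD 1.98 and 21 per group, with the SD of change derived from that correlation. No inflation of type I error is shown. The point deserves correction because the change is cheap and the documents do not rule out the unfavourable end of the range.

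**What to change.** In the Statistical analyses and RQ1 efficacy sections, name the PA-versus-sham difference in RS2-RS3 change as the single primary contrast for each primary outcome. Test it first and outside the Holm family, at an alpha stated for that outcome; the protocol does not say how alpha is shared between the two outcomes, so this must be written down. Apply Holm only to the remaining within-group contrasts and label them secondary.

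The primary contrast must be the between-arm one. Promoting the PA-arm change alone would not test the stated hypothesis of greater reduction with PA than with sham.

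If the 16-member family is kept instead, restate the power at the Holm threshold and give the assumed SD of change or correlation.

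The cost is wording only, with no extra data. The downside is that the other contrasts become secondary.

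### Persistence of benefit on the primary outcomes is examined by within-arm contrasts only; no PA-minus-sham comparison is named at RS4, LTFU1 or LTFU2

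*Protocol article*

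**What the plan says.** The Design section gives RS3 and RS4 two purposes: to compare PA with sham, and to judge "whether any benefits of treatment are maintained at 4 weeks after treatment". RQ3 asks how long any benefit lasts, and the primary research question says the sham arm is there to isolate the true effect of PA.

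The RQ1 analysis section sets out how this is done for the two primary outcomes:

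- Pain: a 2 x 6 Group x Time ANOVA plus sixteen a-priori contrasts (eight visit pairs in each of two arms). The pairs are RS1 vs RS2, RS2 vs RS3 and "RS3 vs. RS4, RS2 vs. RS4, RS2 vs. LTFU1, RS4 vs. LTFU1, LTFU1 vs. LTFU2, and RS2 vs. LTFU2 within each group".
- CRPS severity score: a 2 x 4 ANOVA plus eight contrasts (four visit pairs in each arm), again within each arm.

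The Statistical analyses section applies "Holm-Bonferroni corrections for multiple comparisons within each outcome analysis". No contrast between arms at RS4, LTFU1 or LTFU2 is named for pain, and none at RS4 for the severity score. The number needed to treat does compare arms, but only for RS2 to RS3. Contrasts for group differences by time point are named for the daily logbook ratings only.

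**The concern.** There are two weaknesses, and the first is the main one.

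**No comparison with sham after RS3.** A within-arm change from RS2 mixes the effect of PA with everything else that moves pain over the same weeks: natural course, placebo response and regression to the mean. The last is plausible here, because a current pain score of at least 2 is an entry condition at both RS1 and RS2, and RS2 is also the reference for change. Sham was included to remove these influences, but the named contrasts do not use it. A significant change in the PA arm beside a non-significant one in the sham arm would not show that the arms differ. The reverse error is also possible: if both arms worsen after RS3, PA can look as if its benefit has gone while its advantage over sham is intact.

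**Post-treatment pairs.** RS3 vs RS4, RS4 vs LTFU1 and LTFU1 vs LTFU2 look for loss of benefit. For these pairs a non-significant result is the welcome one, and a stricter alpha makes it easier to obtain. At this sample size, non-significance says little about whether benefit was kept.

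At stake is the answer to RQ3 on the primary outcomes, which is a stated aim although not the primary endpoint.

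**Working it through.** **1. The plan's own figure.** From the Sample size section: a 2-point change in pain ("The sample size required to detect a pain reduction of this magnitude between RS2 and RS3 was estimated"), type I error 5%, "giving 90% power to detect a significant change in the pain", and "The standard deviation expected in the current study was estimated as 1.98 based on pain intensity ratings". Two-sided normal approximation:

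n per arm = 2 x (1.960 + 1.282)² x 1.98² / 2² = 2 x 10.51 x 0.980 = 20.6, rounded up to 21, or 42 in total.

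This reproduces the stated number. Power at 21 per arm is 90.5% by this approximation and 89.1% with the t distribution. The calculation covers RS2 to RS3 only.

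**2. Assumptions for the later visits.** The protocol gives no SD of change and no between-visit correlation r. I take SD 1.98 at every visit, equal correlation between all visits, no missing data and 21 in the arm. Then SD of change = 1.98 x √(2(1 − r)). If 1.98 is itself the SD of change, that is the r = 0.5 row.

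**3. Why a within-arm contrast cannot answer the question.** Suppose both arms are 2 points below RS2 at RS4 for reasons unrelated to PA. The PA effect is 2 − 2 = 0. Yet the PA arm's RS2 vs RS4 contrast, at the strictest Holm step (0.05/16 = 0.003125) and r = 0.5, is significant with about 88% power.

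**4. Chance of missing a 1-point loss from RS3 to RS4 in the PA arm** (half of a 2-point benefit). Paired t-test, non-centrality = √21 x 1 / SD of change. The full-Holm column simulates all sixteen contrasts, 10,000 trials per row: PA falls 2 points at RS3 and retains 1 point from RS4 onwards; sham is flat.

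| r | SD of change | missed at 0.05 | missed at 0.05/16 | missed, full Holm |
|---|---|---|---|---|
| 0.25 | 2.42 | 56% | 90% | 89% |
| 0.5 | 1.98 | 40% | 81% | 81% |
| 0.7 | 1.53 | 19% | 61% | 60% |
| 0.8 | 1.25 | 6% | 38% | 35% |
| 0.9 | 0.89 | <1% | 5% | 4% |

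With the pooled ANOVA error instead of the paired error, the full-Holm figures are about 85%, 74%, 48%, 22% and 1%.

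**5. Would such a trial look like maintained benefit?** In the same simulation (paired error), the pattern of RS3 vs RS4 non-significant together with RS2 vs RS4 significant occurs in about 11%, 18%, 29% and 26% of trials at r = 0.25, 0.5, 0.7 and 0.8. RS2 vs RS4 alone is significant in about 11%, 20%, 41% and 65%.

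**6. Precision of the alternative.** 95% half-widths:

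- PA minus sham, change from RS2: 2.021 x SD of change x √(2/21) = 1.46, 1.23, 0.96 and 0.78 points at r = 0.3, 0.5, 0.7 and 0.8.
- Change since RS3 within an arm: 2.086 x SD of change / √21 = 1.07, 0.90, 0.70 and 0.57 points at the same r.

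The between-arm comparison at two-sided 0.05 has 77%, 89%, 98.5% and over 99% power for a retained 2-point difference, and 27%, 36%, 54% and 71% for a retained 1-point difference.

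No figures are given for the severity score, because the protocol gives no SD for it.

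**The case against.** The case on the other side is substantial.

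- **Maintenance does not rest on non-significance alone.** The quoted list includes RS2 vs RS4, RS2 vs LTFU1 and RS2 vs LTFU2, where significance is the favourable result and Holm is conservative. The protocol also uses pre-treatment as its reference elsewhere: it expects a return to that level over time, and counts days to it in the logbook analysis. This stands. It does not meet the main point, because these contrasts too are within one arm.
- **No rule equates p > 0.05 with maintenance.** A reader might infer that the trial would probably report a half-lost benefit as maintained. The protocol does not say so, and step 5 does not support it: the pattern needed occurs in fewer than a third of trials. At low correlations the usual result is that no benefit is shown at RS4.
- **The miss rates depend on an unstated correlation.** This stands. They fall below half at r of about 0.8, at 0.7 with the pooled error, and from about 0.4 without Holm.
- **The Group x Time ANOVA compares the arms, and significant interactions are to be followed up by contrasts.** True, but the interaction spans all visits and can be driven by RS3, and the contrasts actually named are within-arm.
- **Carrying RS2 forward exaggerates loss in an arm that improved.** True where visits are missing, but it does not supply a comparison with sham.
- **A margin for maintenance is commonly left to a fuller document.** Agreed. No margin is asked for here.

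**Conclusion.** The point holds in a limited form. For both primary outcomes, the contrasts that bear on lasting benefit are fixed as within-arm, and no PA-minus-sham comparison is named at RS4, LTFU1 or LTFU2. This follows from the text and needs no assumption. The omnibus interaction does not fill the gap.

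Second, a non-significant change between post-treatment visits cannot be read as maintenance. For pain, a 1-point loss would be missed in about 60% to 90% of trials for r from 0.7 down to 0.25, and in about 35% at r = 0.8. This rests on 21 in the arm, SD 1.98 at all visits, equal correlations, complete data and paired error.

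It is not established that false maintenance is the likely result. The RS2 to RS3 endpoint, for which the trial is sized, is outside this point. The change is worth making because maintenance is a stated aim and the remedy needs no new data.

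**What to change.** 1. For pain, report the PA-minus-sham difference in change from RS2 at RS4, LTFU1 and LTFU2, each with a 95% CI. For the severity score, do so at RS4. Base statements on lasting benefit on these differences.
2. Report change since RS3 within each arm as an estimate with an unadjusted 95% CI. Take RS3 vs RS4, RS4 vs LTFU1 and LTFU1 vs LTFU2 out of the Holm families.
3. State that a non-significant change since RS3 will not be interpreted as maintenance.

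The cost is a change of analysis wording; no data or visits are added. Removing three pairs in two arms cuts the pain family from 16 to 10 (16 − 3 x 2), and removing one pair cuts the severity family from 8 to 6 (8 − 1 x 2), which also eases the RS2 vs RS3 contrasts. The downside is width: with between-arm half-widths of about 1.0 to 1.5 points for r = 0.7 to 0.3, a retained 1-point advantage would often be inconclusive.
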